### Participants

The target sample for each group (intervention and control) is 165 participants, 330 participants in total. The clinical centres selected are those in which the scientific partners are affiliated. Patients from the clinics are referred to the study by their treating physicians, who are also responsible for the patients throughout the trial.

#### Inclusion criteria

Eligible participants are adults aged 18 or older with a diagnosis of one of five following somatic conditions: MI; breast cancer; prostate cancer; kidney failure; and leg amputees. The participants must also be proficient in the language of the country where recruited.
Patients with myocardial infarction are included if there is a diagnosis of (MI) type I including chest pain for more than 20 min (or equivalent symptoms), acute ECG alterations, and a diagnostic increase of myocardial necrosis biomarkers.Breast cancer patients are recruited either at stage II, III or IV.Prostate cancer patients are recruited either at stage II, III or IV.Kidney failure patients are recruited if they are in a stable clinical condition with chronic kidney failure of stages III, IV, and V as defined by the KDOQI guidelines. This corresponds to an estimated glomerular filtration rate (eGFR) below 60 mL/min/1.73 m^2^ of body-surface area.Amputee patients are recruited if they have had a lower limb amputation at any level and are within the 6 months post-surgical intervention.

#### Exclusion criteria

Patients are excluded if they have a past diagnosis of a major psychiatric disorder other than depression. These psychiatric disorders include bipolar disorder, psychosis, and suicidality. Therefore, a diagnosis of depression as a disorder or depressive symptoms is not an exclusion criterion. Moreover, patients are excluded if they have had any recent and active severe suicidality as assessed by the Paykel Suicide Scale [17] or if they have been in treatment with a stable drug therapy for less than two months. Patients are also excluded if they have any cognitive impairment, such as dementia. Moreover, individuals are excluded if they have been involved in other structured psychological treatments involving mindfulness, CBT, other relaxation techniques, or other structured psychotherapy within the three months preceding enrolment. An individual is also ineligible if they have participated or are currently participating in any clinical trial including but not limited to pharmacological trials that might interfere with the study objectives. A lack of capability to participate in study procedures including giving consent will also result in ineligibility. Finally, individuals are ineligible if they demonstrate an inability to use Smartphone technology, especially touch screen interaction and basic maintenance procedures of the devices (e.g. includes charging, switching on and off, reading notifications, making calls, and sending and receiving text messages). Patients’ ability to use Smartphone technology was assessed by asking patients whether they are able to use smartphones to check and send emails.

All patients that meet the inclusion criteria are asked to participate after a comprehensive explanation of the study. Patients provide written consent following the guidelines set by the local ethics committee. Once the patients have consented, they are randomised to either the intervention group or the control group. Subsequently, they are asked to complete the baseline questionnaire. The primary outcome is assessed at 12-weeks after baseline assessment, and a follow-up assessment occurs at 24 -weeks.

### Setting and location

Participants are recruited from three different locations; Turin and Pisa in Italy and Lisbon in Portugal. Kidney disease patients are recruited from the Cisanello University Hospital, University of Pisa, Italy. Breast and prostate cancer patients are recruited from the following centres within the Piedmont Oncological Network, at San Luigi Gonzaga University Hospital, Turin, Italy and Breast Unit-Oncology Department and Urology Department at Città della Salute e della Scienza University Hospital, Turin, Italy. Myocardial infarction patients are recruited from the Cardiology Department at the Santa Maria Hospital, Lisbon. Patients with lower limb amputations are recruited at the Rehabilitation Department at the Santa Maria Hospital, Lisbon. Each of the centres will recruit 75 patients, except for the Rehabilitation department in Santa Maria Hospital which will recruit 30 patients with lower limb amputations. The departments in Turin and Lisbon are the main departments for the region, thus, patients come from all over the region to the clinical centres in Turin and Lisbon.

### Intervention group

The intervention group will receive the NEVERMIND system in addition to TAU, which is described in detail in the next section. The NEVERMIND system is a multifaceted, two-component system that comprises a smart shirt and a user interface, in the form of a mobile application, to put patients at the centre of their health management. The system is a real-time decision support system, aiming to predict the severity and onset of depressive symptoms by modelling the well-being condition of patients based on physiological data, body movement, and the recurrence of social interactions.

The interface monitors the patient’s mental health daily and treats mental health issues as they arise. If a user displays symptoms of depression, they are directed to different levels of treatment in the application. Further targeted advice and care is provided if the user displays symptoms of depression, anxiety, or stress, either through targeted mindfulness or through the online cognitive behavioural therapy programme, Deprexis, provided by Gaia AG [18].

The user interface also includes an Avatar and a speech monitoring feature to synthetize the system’s messages. In addition, the interface can be personalised to suit the patient’s dietary requirements, exercise recommendations and preferences to provide lifestyle guidance to improve their physical health tailored to their primary somatic condition. This is set up by the treating physician who also enters medical details including weight, blood pressure, and type of condition into the system. Several components are readily available to the patient upon receiving the system (Fig. 1). Lifestyle factors included in the application include diet tips, including recipes, and information about physical activity, including practice exercises. Moreover, there is a section on sleep hygiene and two mindfulness practices per day, either 10 or 25 min long, which can be chosen by the patient.

**Fig. 1 Fig1:**
[figure not shown]
Components freely available to the patients without activation

The smart shirt collects physiological data (biomedical data) including electrocardiogram (ECG), accelerometer data, and respiration data, from which biomedical features are extracted based on signal processing techniques. These features are from three categories: movement dynamics, ECG-heart rate variability, and respiration dynamics.

The patients are encouraged to use the shirt as much as they like but must use it for a minimum of twice a week. The combined data from the interface and the shirt will trigger different responses encouraging patients to perform or alter activities and lifestyle choices to reduce the occurrence and severity of depressive symptoms based on their likelihood of developing depressive symptoms. Based on the general state of the patients, they can be directed to different levels of care as outlined below.

The levels of care (LC) are:
LC0: Positive feedback for individuals who are managing their mental health and well-being well.LC1: Behavioural advice for those showing initial symptoms of depression, anxiety, or stress.LC2: Targeted mindfulness if mild or moderate symptoms of depression, anxiety, or stress.LC3: Online cognitive behavioural therapy, Deprexis, for those with moderate or severe symptoms of depression, anxiety, or stress.LC4: The treatment team will be contacted if patient displays severe symptoms of depression or insomnia for several days in a row.LC5: Emergency information and contact of the treatment team if the patient has suicidal intent.

If patients are not responding to a specific treatment and are still reporting depressive symptoms after four weeks, they will be asked if they wish to change to another LC. All patients will receive the NEVERMIND system for 12 weeks. Furthermore, each patient in the intervention group will receive a medical consultation regarding diet, physical activity, sleep, and an introductory session to mindfulness.

To encourage the use of the system and to measure adherence, the system has a compliance monitoring system. If a patient is inactive for three days, that is, not answering the daily questions for three days, a reminder will be sent to the patient. If the user is inactive for seven days, that is not using the system for seven days, the user will receive another reminder and the treatment team will be notified, and they will contact the user to ask the reason for inactivity. If the reason for inactivity is the inability to manage their depressive symptoms, the users will be referred to further treatment.

### Control group

The control group will receive TAU per the standard guidelines at the respective clinics. In the Nephrology ward at the Pisa University Hospital, patients undergo clinical consultations with physicians regularly. The frequency is based on the type of disease and stage of disease of each patient. For patients in pre-dialysis, the visit is scheduled monthly, for patients in dialysis, the visit takes place before every dialysis session, often three times a week. During the visit, an evaluation of mood and anxiety symptoms is performed. If patients report a change in mood or an increase in anxiety level, a visit with a psychiatrist is scheduled within one week. If necessary, medication is prescribed for patients for the relevant psychiatric symptomatology which is compatible with the clinical status of the patient.

In the clinics in Turin, TAU in terms of preventing and treating comorbid mental illness consists of standard clinical management. This includes clinical interviews with the oncologist and eventual referral to the consultation-liaison service, providing assessment, and, if necessary, medications or brief psychological support or both.

The Santa Maria Hospital in Lisbon is a tertiary care unit which has no specific protocol for treating mental health problems. There is a liaison psychiatrist and a liaison psychologist in each of the clinical departments with whom a patient can meet on request. However, treatment for mental ill-health is usually given to patients at the primary care level within the local hospital. Patients receiving psychiatric consultation and medication for depression are retained in the trial.

### Standardisation of intervention administration

Each patient participating in the intervention group receives the standardised NEVERMIND system. All components provided are managed at a central level. The smart shirt and the docking station are distributed by Smartex, and patients are issued the same smartphone with the same user interface. The smart shirt undergoes quality control before it is distributed to the patients. This is done by sending the data through the docking station to the server where the data quality control is checked by looking at the quality of signals received at the docking station. The smartphone is set up so that patients can only use it for the NEVERMIND application. All clinicians and other care providers in both the intervention and control groups are informed to perform TAU only.

### Outcomes

#### Primary outcome

Hypothesis: NEVERMIND will significantly decrease the level of depressive symptoms in the intervention group in comparison to TAU in the control group;

Outcome measure*:* the severity of depressive symptoms as measured by the Beck Depression Inventory II (BDI-II) at T12 (12-weeks post baseline assessment).

#### Secondary outcomes

Secondary outcomes to be measured include general well-being, patient self-efficacy management of primary somatic condition, perceived stigma, prevention of depressive symptoms, and sustainability of the effect of NEVERMIND at 24-weeks post-baseline assessment.

#### Evaluation procedures

Data will be collected at baseline, at 12 and 24 weeks using self-report questionnaires. Moreover, there will be a clinical interview at baseline and at each follow-up. The presence of a psychiatric diagnosis according to DSM-V criteria will also be evaluated during the interview. DSM diagnosis are ascertained by an interview with a psychiatrist at baseline.

The scales that will be administered at baseline and at each follow-up evaluation include the following rater-based and self-report scales:
the *Beck Depression Inventory II (BDI-II)* which measures depressive symptoms [19]the *Hamilton Rating Scale for Depression (HAM-D)* which measures depressive symptoms [20]the *Depression, Anxiety and Stress Scale (DASS-21)* which measures depressive, anxiety, and stress symptoms [21]the *Hamilton Rating Scale for Anxiety (HAM-A)* which measures anxiety symptoms [22]*WHO Well-being Scale (WHO-5)* which evaluates mood, vitality, and general interests [23]the *Paykel Suicide Scale (PSS)* which determines suicidal ideation and behaviour [17]the *Chronic Illness Anticipated Stigma Scale (CIASS)* which measures perceived stigma [24]the *Self-Efficacy for Managing Chronic Disease Scale* which evaluates self-efficacy in managing a chronic disease [25]the *Neuro-QoL (Quality of Life in Neurological Disorders) Satisfaction with Social Roles and Activities (8-item)* which assesses satisfaction with daily life when living with a chronic illness [26]the *Brief Illness Perception Questionnaire* which assesses illness perception [27]the *Self-Compassion Scale (Short Form)* which measures self-compassion [28]*the Rapid Assessment of Physical Activity (RAPA)* which assesses levels of physical activity [29]

The following socio-demographic data will be collected at baseline: age, sex, education, marital status, employment, socioeconomic status, living arrangement, and nationality.

#### Sample size

The NEVERMIND system was newly developed and is tested in this study for the first time. Therefore, we could not base the sample size calculations on a previously measured effect size. We estimated the sample size based on a previous study that evaluated the effectiveness of Deprexis in reducing depressive symptoms among patients with somatic disorders [30]. A very similar effect size was also found in a meta-analysis that looked at the effectiveness of Deprexis for depressive symptoms in different settings [18]. The sample size was calculated to detect a similar reduction in depressive symptoms (d = 0.54), where a linear mixed model analysis will be used with a power of 80%, two groups, an intercorrelation coefficient of 0.5 and a significance level of 0.05 (sistas-package [31] and lme4-package [32] for the primary outcome. According to power calculations performed with R [33] for the proposed linear mixed model analysis, 110 patients were estimated. Based on the recruitment criteria, which do not stipulate depressive symptoms as an inclusion criterium, we acknowledge that not all patients will exhibit depressive symptoms at recruitment. Therefore, the sample size was adjusted to account for this. We assume that at least 1/3 of the subjects in the sample of patients with chronic conditions will have depressive symptoms at baseline. In order to reach the desired sample size of 110 patients with depression or depressive symptoms, a sample of 330 subjects who complete the study is required to have adequate power to detect medium effects. A drop-out rate of 20% has been accounted for by adjusting the recruitment process.

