#### Statistical analysis

Intention-to-treat (ITT) analysis will be carried out, which hypothesises the superiority of the NEVERMIND system in reducing depressive symptoms in comparison to TAU. A linear mixed model will be used in order to use all available data of each subject and choose an appropriate covariance structure reflecting the potential dependence due to repeated measures. In order to account for the repeated measurements, the baseline measures will be adjusted for in the model [30, 34]. This increases statistical power, accounts for regression towards the mean, and has been recommended for longitudinal analysis of RCTs [35, 36]. Therefore, the ITT for the primary outcome (BDI-II score at 12-weeks) will be used as recommended for statistical analysis of clinical trials by the European Medicines Agency (EMA; codes CPMP/ ICH/363/96 and CPMP/EWP/2863/99). Group (intervention and control), disease type, and hospital will be included as fixed factors.

Comparison of demographic and clinical characteristics at baseline between subjects of varying primary somatic conditions and clusters as well as between intervention and control group will be examined. In case of imbalances of some characteristics, explorative sub-group analyses will be performed.

If a difference between ITT and per-protocol analysis is observed, more weight will be given to the ITT analysis, which is seen as the primary analysis. If the NEVERMIND system does not show superiority effect over treatment as usual for the ITT analysis, we will look at the extent of usage of the different components of the NEVERMIND system. Additionally, secondary analyses of the primary outcome will include per-protocol evaluations and examine the preventive effect of the NEVERMIND system on the incidence of depression (sensitivity analysis). Analyses of the other secondary outcomes (quality of life, perceived stigma and self-efficacy) will be examined in a similar manner.

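### The stated 80% power belongs to a comparison within 110 patients with depressive symptoms, not to the planned primary ITT test in all 330 patients

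*Protocol article*

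**What the plan says.** The Sample size section borrows its effect from a study of Deprexis in patients with somatic disorders: "The sample size was calculated to detect a similar reduction in depressive symptoms (d = 0.54"). The other settings are "a linear mixed model analysis will be used with a power of 80%, two groups" and "an intercorrelation coefficient of 0.5 and a significance level of 0.05". This gives 110 patients. The section then notes that symptoms are not required for entry and continues: "We assume that at least 1/3 of the subjects in the sample of patients with chronic conditions will have depressive symptoms at baseline". From this it derives the requirement: "In order to reach the desired sample size of 110 patients with depression or depressive symptoms, a sample of 330 subjects who complete the study".

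The Primary outcome section names BDI-II severity at 12 weeks. The Statistical analysis section fixes the test: "Intention-to-treat (ITT) analysis will be carried out, which hypothesises the superiority of the NEVERMIND system in reducing depressive symptoms in comparison to TAU". It is a linear mixed model adjusted for baseline, with group, disease type and hospital as fixed factors. Neither section limits the primary comparison to patients with symptoms at baseline. The only subgroup analyses mentioned are exploratory and depend on baseline imbalance.

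**The concern.** By the protocol's own reasoning, d = 0.54 is an effect in patients who have depressive symptoms. Had it been expected in all comers, 110 patients would have been enough and there would have been no reason to triple the number. The tripling secures 110 symptomatic patients, but the primary test does not analyse those 110 on their own. It averages the effect over everyone, including up to two thirds assumed to be without symptoms at entry. Nothing is said about the effect or the BDI-II SD in that mixed population.

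If the average effect is well below 0.54, the system could perform as hoped in symptomatic patients and still miss significance on the primary test. Readers would then credit that null result with 80% power, although the document does not show that the test had it.

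**Working it through.** **Inputs from the protocol article.** d = 0.54, power 80%, alpha 0.05, correlation 0.5, 110 patients, at least 1/3 symptomatic, 330 completers and 20% drop-out (all Sample size); 165 per arm (Participants).

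**Assumptions, not in the documents.** The test is two-sided (this reproduces the 110). The SD is common to all patients. Exactly 1/3 are symptomatic. Patients without symptoms gain a fraction f of 0.54. The stated 0.5 is taken as the baseline-to-week-12 correlation r.

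**1. The plan's own figure.** A two-sample t-test for d = 0.54 at 80% power needs 54.8, so 55, per arm: 110 in total. The normal approximation gives 2 × (1.960 + 0.842)² / 0.54² = 53.8, so 54 per arm and 108. A change score at r = 0.5 has variance factor 2(1 − 0.5) = 1 and gives the same. Baseline adjustment, with factor 1 − 0.5² = 0.75, would give 82. The 110 therefore reproduces as an unadjusted calculation, and 110 / (1/3) = 330 is exact.

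**2. Average effect in all patients.** d_avg = 0.54 × (1/3 + (2/3) × f):
- f = 0: 0.18
- f = 0.25: 0.27
- f = 0.5: 0.36

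**3. Number analysed.** The article gives 330 both as the completers required and as the target sample (75 × 4 + 30 = 330 in Setting and location). If 330 are recruited and 20% drop out, 330 × 0.8 = 264 remain, or 132 per arm. Both cases are shown.

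**4. Power of the all-patient test.** The noncentrality is (d_avg / √v) × √(n/2), with n per arm, v = 1 unadjusted and v = 0.75 baseline-adjusted. For f = 0 and n = 165 it is 0.18 × √82.5 = 1.63 unadjusted and 1.63 / 0.866 = 1.89 adjusted.

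| Gain in patients without symptoms | d_avg | 330 analysed: unadjusted / adjusted | 264 analysed: unadjusted / adjusted |
|---|---|---|---|
| none | 0.18 | 37% / 47% | 31% / 39% |
| a quarter of 0.54 | 0.27 | 69% / 81% | 59% / 71% |
| half of 0.54 | 0.36 | 90% / 96% | 83% / 92% |

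**5. Sensitivity to the assumptions.**
- If half the patients are symptomatic and the rest gain nothing, d_avg = 0.54 × 0.5 = 0.27, which is the second row.
- If patients without symptoms gain nothing but have half the SD, the average variance is 1/3 + (2/3) × 0.25 = 0.5. Adjusted power is then 76% (330) or 66% (264).
- If d = 0.54 held in everyone, power with 330 would be 99.8% even unadjusted.

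**6. Detectable all-patient difference at 80% power.** Unadjusted, 2.802 × √(2/165) = 0.31 SD with 330 and 2.802 × √(2/132) = 0.345 SD with 264 (0.346, so 0.35, by the t-test). Multiplying by 0.866 for baseline adjustment gives 0.27 and 0.30 SD. With 330 analysed, the gain needed in patients without symptoms is (0.31/0.54 − 1/3) / (2/3), about 36% of the symptomatic effect, or about 24% with adjustment.

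**7. Power within the symptomatic patients.** With 55 per arm it is 80% unadjusted, as stated. A third of 264 is 88, or 44 per arm, for which the same unadjusted t-test has about 71%.

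**The case against.** The best defence is that low power follows only from an extreme assumption. The protocol does not say that patients without baseline symptoms cannot benefit. Prevention of new symptoms is a secondary objective. Lifestyle guidance, sleep hygiene and mindfulness are available to every user, and the stepped levels of care also respond to anxiety and stress. One third is stated as a minimum. A modest gain in the other patients, or a larger symptomatic share, brings the adjusted power with 330 analysed to about 81%. The article also admits that no effect size for this system existed, and its Limitations section calls the trial a pilot giving an initial indication.

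This stands as far as the size and direction of the error go. Four stronger readings are tempting but not supported:
- *That the trial is underpowered.* The effect outside the symptomatic group and the mixed-population SD are not given, so the power could lie on either side of 80%.
- *That two thirds of the patients have nothing to treat.* The prevention objective and the components open to all contradict this.
- *That the symptomatic analysis would go unreported.* The full protocol and any SAP are not shown. One can say only that the article does not plan it.
- *That d = 0.54 is invalid because of the rule "LC3: Online cognitive behavioural therapy, Deprexis, for those with moderate or severe symptoms of depression, anxiety, or stress".* The article openly uses Deprexis as a proxy. The rule adds some doubt about carrying the effect over, but shows no error.

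The defence does not remove the mismatch. The article fixes both the powered population and the tested population, and they differ. It makes no claim about the effect in patients without symptoms that could bridge them.

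**Conclusion.** The point holds as a mismatch between the power statement and the primary test. The arithmetic behind 110 and 330 is correct, but its 80% describes a comparison within 110 symptomatic completers, and the article justifies no power for the all-patient ITT test.

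Under a common SD, one third symptomatic and r = 0.5, baseline-adjusted power runs from 47% to 96% with 330 analysed, and from 39% to 92% with 264, as the gain in the other patients goes from none to half of 0.54. A larger symptomatic share or a smaller SD in patients without symptoms raises these figures. The ITT test itself remains valid. This should be fixed, but it is a fault in the justification and not in the comparison.

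**What to change.** Keep the all-patient ITT comparison as primary and change the following:

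1. Restate its power in the Sample size section as 80% for an all-patient difference of about 0.27 SD with 330 analysed, or 0.30 SD with 264, assuming baseline adjustment at r = 0.5 (0.31 and 0.35 SD unadjusted). Show the range of power by assumed gain in patients without symptoms, with the assumptions named.
2. State that 80% at d = 0.54 applies only to a comparison within 110 symptomatic completers, and falls to about 71% unadjusted if there are 88.
3. Pre-specify as the first secondary analysis the week-12 group effect in patients at or above a baseline BDI-II cut-off, fixed before unblinding. Fit it in a model separate from the primary one, so that the primary group effect keeps its meaning. Add a group by centred baseline BDI-II interaction as a supporting analysis.

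The cost is revised wording and one extra analysis with its supporting model. BDI-II is already collected at baseline, so no new data or patients are needed. The drawback is that the stated power becomes less favourable.

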## Background

Depressive disorders are one of the leading causes of the burden of disease globally. It is the third leading cause of disability worldwide [1] with an estimated one-year prevalence of depression of approximately 3% in the general population [2]. This increases significantly in individuals with severe somatic conditions as there is a high likelihood of developing a comorbid mental illness. The prevalence of depressive symptoms in patients who have suffered acute myocardial infarction (MI) is estimated at 14% [3] while the prevalence in individuals with chronic kidney disease can range between 26 and 39% [4]. Depressive symptoms are defined as symptoms experienced by patients as identified with self-reported or rater-based scales. Depression, as confirmed with a clinical diagnosis and/or identified with ICD codes, in patients with chronic kidney disease has a prevalence that ranges between 21 and 22.8% [4], and between 3 and 28% in cancer patients depending on the cancer type and treatment phase [5]. However, in reality, these estimates are likely to be higher as depression is often under-reported and under-detected [6]. Moreover, these estimates do not account for other comorbidities, which have been shown to increase the risk of depression. A review of the literature on chronic conditions and comorbid depression found 1.7 increased odds of depression in patients with more than one chronic illness compared to patients with only one chronic illness [7].

This added burden of disease increases the strain felt by the patient, impacting the outcome of the primary disease [8] as well as quality of life (QoL) [2], and thereby can result in a reduction in the management of symptoms [6]. A meta-analysis assessing the impact of depression on mortality after MI indicated that patients who develop depression after MI are at a 13% increased risk of subsequent cardiac events and 22% increased risk of all-cause mortality [9]. In addition to the burden on the patient, there is an added burden on the healthcare system. It has been estimated that cancer patients with comorbid depression have a 32% higher healthcare expenditures and are more likely to use emergency care compared to patients who do not have comorbid depression [10].

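### The sample-size section needs 330 completers and says 20% drop-out is covered, but the only study size and recruitment total given is also 330, so no allowance is visible

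*Protocol article*

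**What the plan says.** All references are to the protocol article.

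- **Sample size, effect and error rates.** "The sample size was calculated to detect a similar reduction in depressive symptoms (d = 0.54") by a linear mixed model "with a power of 80%, two groups, an intercorrelation coefficient of 0.5 and a significance level of 0.05". The result: "According to power calculations performed with R [33] for the proposed linear mixed model analysis, 110 patients were estimated".
- **Sample size, prevalence step.** Depressive symptoms are not an entry criterion, so the 110 are scaled up: "We assume that at least 1/3 of the subjects in the sample of patients with chronic conditions will have depressive symptoms at baseline". This gives 330, which the section describes as the number who must finish the study.
- **Sample size, drop-out.** "A drop-out rate of 20% has been accounted for by adjusting the recruitment process".
- **Participants.** "The target sample for each group (intervention and control) is 165 participants, 330 participants in total".
- **Setting and location.** "Each of the centres will recruit 75 patients, except for the Rehabilitation department in Santa Maria Hospital which will recruit 30 patients" with lower limb amputation.
- **Abstract, Methods.** The study is described as including 330 patients.

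No recruitment number above 330, and no rule for replacing patients or recruiting beyond the target, appears in the article.

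**The concern.** One number is given two meanings. In the Sample size section, 330 is what must remain after losses. In the abstract, the Participants section and the recruitment quotas, 330 is what goes in. With 20% expected to leave, both cannot be true.

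The reader is told that drop-out has been dealt with and that the power is 80%. If 330 is the number randomised, neither statement follows from the figures given. This bears most on a null result, which would be read against a power that the stated numbers do not deliver.

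**Working it through.** **Inputs.** From Sample size: d = 0.54, power 80%, significance level 0.05, correlation 0.5, symptomatic share 1/3, drop-out 20%. From Participants: 330 in total, 165 per group. From Setting and location: quotas of 75 and 30. The article does not say whether the test is one- or two-sided; two-sided is assumed here.

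**Step 1. Reproduce 110.** A two-sided two-sample t-test with d = 0.54 and 80% power needs 54.8 per arm, so 55 per arm and 2 × 55 = 110. Power at 55 per arm is 80.1%. The normal approximation gives 54 per arm, 108 in total. Two other routes miss 110: a one-sided test (normal approximation) gives 86, and baseline adjustment with r = 0.5 gives about 83 (step 6). The 110 is therefore what a plain two-group comparison gives, without the correlation.

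**Step 2. Reproduce 330.** 110 ÷ (1/3) = 330. The prevalence step uses the whole of 330, and nothing is left for drop-out.

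**Step 3. Recruitment total.** Four units of 75 plus the amputee unit: 4 × 75 + 30 = 330. This equals the total in the abstract and in Participants.

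**Step 4. What the allowance would require.** 330 ÷ (1 − 0.20) = 412.5, so 413 randomised.

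**Step 5. What 330 randomised would give,** with all the loss before week 12:

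- completers: 330 × 0.80 = 264
- symptomatic completers at 1/3: 264 ÷ 3 = 88, or 44 per arm
- shortfall: 110 − 88 = 22
- symptomatic share needed to reach 110: 110 ÷ 264 = 41.7%

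**Step 6. Power for d = 0.54.** Baseline adjustment with r = 0.5 multiplies the residual SD by √(1 − 0.5²) = √0.75, so the effective d is 0.54 ÷ √0.75 = 0.624.

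| Symptomatic patients | t-test that reproduces 110 | With r = 0.5 as baseline adjustment |
|---|---|---|
| 110 (55 per arm) | 80% | 90% |
| 99 (49.5 per arm) | 76% | 87% |
| 88 (44 per arm) | 71% | 82% |

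In the right-hand column, 80% power needs 41.4 per arm, about 83 patients in total, so 110 is not the 80% requirement on that basis.

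**Step 7. Timing of the loss.** The primary outcome is at week 12 and follow-up runs to week 24; the article does not say by when the 20% applies. If half of it fell after week 12 (an assumption), 330 × 0.90 = 297 would supply the primary outcome and 297 ÷ 3 = 99 would be symptomatic. That is the middle row of the table.

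**The case against.** **The allowance may have been made.** The article says that recruitment was adjusted, and it condenses a fuller protocol. Recruiting until 330 had completed would fit that sentence. This stands as a possibility, and it is why one cannot say that no allowance was ever made. But the article gives no number or rule for it, and its quotas are worded as patients to recruit. If over-recruitment was the plan, the totals elsewhere are wrong, so the text needs correcting on either reading.

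**The quotas might sum to more.** One Turin hospital contributes two departments. Counting each as a unit gives 5 × 75 + 30 = 405, close to 413. That reading contradicts the 330 in the abstract and in Participants, whereas four units of 75 match it exactly. The wording is loose enough to need tidying.

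**Power may still be adequate.** The stated method is a mixed model with correlation 0.5, not a t-test. If that correlation is credited as baseline adjustment, 88 patients give about 82%. This is correct, so 71% must not be called the power on the stated method. It is the power on the calculation that reproduces 110. Crediting the correlation lowers the requirement to about 83 and leaves 110 unexplained. In addition, both figures refer to a symptomatic subset, while the planned primary analysis is intention-to-treat on all patients, so neither is the power of that analysis.

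**The loss may be smaller at week 12.** This also stands: 264 and 88 assume that the whole 20% is gone by then.

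**A tempting extension.** A reader might infer that the Background prevalences disprove the assumption of at least one third. They do not. One third lies inside the 26–39% quoted for kidney disease. The 3–28% quoted for cancer is diagnosed depression, not symptoms. No figure is given for amputees, and the Background itself says that the estimates are probably low. No disease-specific count or power can be built on them.

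**Conclusion.** The drop-out statement is wrong as written: the article's figures show no allowance, because 330 serves both as the completers required and as the total to recruit.

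If 330 are randomised, 20% are lost before week 12 and one third are symptomatic, the design yields about 88 symptomatic completers against the 110 required, a shortfall of 22. Power is then about 71% on the t-test that gives 110, or about 82% with r = 0.5 credited against a requirement of about 83. With half the loss after week 12, the shortfall is 11 (99 against 110) and the t-test power 76%.

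The documents do not support the stronger conclusion that the trial is underpowered. That depends on which calculation is credited, when patients leave and whether more than 330 are in fact recruited. A symptomatic share of 41.7% or more would also offset the loss, but that is not the planning assumption. What is established is that the stated numbers contradict each other and that the claim of covered drop-out cannot be derived from them.

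**What to change.** In the abstract, Participants, Setting and location and Sample size sections, state the number randomised separately from the number expected to complete, and say by which visit the 20% applies.

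- **If 330 is the number randomised:** delete the claim that 20% drop-out is covered. Give the expected completers (about 264), the expected symptomatic completers (about 88 at one third) and the matching power, naming the calculation and the correlation: about 71% for a two-sample t-test, or about 82% with baseline adjustment at r = 0.5. If the second is used, also restate the 110, because about 83 would then be the 80% requirement.
- **If 330 completers was the intent and recruitment already exceeds 330:** correct the totals in the abstract, Participants and Setting and location (413 randomised at 20% loss), with quotas that add up to the new total.

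The cost is rewording in four places. On the first reading the power stated may be less favourable. No extra enrolment is asked for, and no trial procedure changes.
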